## Abstract

**Background:**

It is estimated that 19 to 83% of people with dementia suffer from pain that is inadequately treated in the last months of life. A large number of healthcare workers who care for these people in nursing homes lack appropriate expertise and may therefore not always recognise, assess and treat pain in those with dementia who have complex problems on time, properly and efficiently. The aim of this intervention trial is to identify care needs of people with dementia suffering from pain living in a nursing home.

**Methods:**

A quasi-experimental nurse-led intervention trial based on a convenience sample of four nursing homes in the Swiss Canton of Zurich examines the effects on dementia patients (*n* = 411), the healthcare institution and the qualification level of the healthcare workers compared to historical controls, using an event analysis and a multilevel analysis. Healthcare workers will be individually trained how to assess, intervene and evaluate acute and chronic pain. There are three data-monitoring cycles (T0, T1, T2) and two intervention cycles (I1, I2) with a total study duration of 425 days. There is also a process evaluation based on Dobbins analyses that analyse in particular the potentials for change in clinical practice of change agents.

**Discussion:**

The aim of the intervention trial is to improve pain management strategies in older people with dementia in nursing homes. Clinically significant findings will be expected that will help reduce suffering in the sense of “total pain” for people with dementia. The joint intra- and interdisciplinary collaboration between practice and supply-oriented (nursing) research will have both a lasting effect on the efficiency measurement and provide scientifically sound results. Nursing homes can integrate the findings from the intervention trial into their internal quality control process. The potential for improvements can be directly influenced by the nursing home itself.

**Trial registration:**

Registration trial number: DRKS00009726 on DRKS, registered 10 January 2017, retrorespectively registered. Clearance certificate is available of the ethics committees of the canton of Thurgau, Switzerland, number: TG K201-02, and Zurich, Switzerland, number: ZH 01–2016.

## Background

Approximately 25% of people over the age of 85 years in Switzerland live in retirement and nursing homes. The average length of stay is 2.6 years [1]. More than half the people in nursing homes live with symptoms of dementia or have been diagnosed with dementia [2]. People with dementia show the characteristic symptom manifestation: 1) shortness of breath often combined with respiratory infections leading to pneumonia; 2) pain and 3) behavioural disorders, in particular agitation, restlessness and disorientation [3–13].

Of those people with dementia, 19–83% suffer from pain [7, 8, 10, 14–16] that is inadequately treated in the last months of life [17, 18]. The Pallhome study conducted in Switzerland identified pain and behavioural problems, as causing the greatest difficulties in controlling symptoms in dementia patients in nursing homes [19]. However, the fact that both symptoms can occur simultaneously makes it difficult to differentiate them [20, 21]. Zwakhalen and colleagues [14] also detected an increased risk of pain for people with multiple concurrent health problems and for people taking several analgesics. Both factors are true for people suffering from dementia in nursing homes. Untreated pain can lead to depression, sleep disorders, falls, malnutrition and deterioration in daily activities and physical functions [22]. In this context, various barriers to the treatment of pain in people with dementia have been identified [23–27] including: inadequate knowledge about the relationship between pain and behaviour; interpretation of behaviour; intensity of pain; pharmacological interventions and their side effects; non-pharmacological interventions; and interventions without prior clinical assessment by professionals. In addition, organisational frameworks such as the definition of responsibilities, the physicians’ claim that the patient had no pain and high staff turnover have been identified as barriers relevant to effective pain management [23, 25–28].

A daily diary for the detection and review of disease progression is considered an effective non-pharmacological intervention for pain. Primary nurses are present in nursing homes 24 h a day, 7 days a week, which means that they have detailed knowledge of the dementia patient, their needs and responses. They are therefore perfectly suited to assess the pain situation of older people in nursing homes. Equally important are individually tailored daily activities with one-to-one patient care, sufficient food and drink, breathing exercises and ergonomic adjustments in daily activities [24, 29]. The trial and error method can help to find out whether an analgesic helps or not when the presence of pain is unclear [24]. Case discussions are also used in everyday clinical practice. Their effectiveness has already been studied in the long-term care of dementia patients [30]. Hence they may be integrated as additional instruments in everyday life in nursing homes, but they are only conducted weekly or less often. Preliminary evidence shows that it is possible to provide care by qualified nursing staff that are continuously present, are suitably qualified, collaborate in interdisciplinary ways, and have target group-specific advanced knowledge. In addition, collaboration between nursing home physicians and advanced practice nurses in long-term care facilities have proven to be successful [31, 32].

As many as 52% of healthcare workers in Swiss nursing homes currently have no training or are employed at assistant level and have to cope with the complex needs of people with dementia [33]. Specific knowledge of pain assessment and management in everyday clinical situations in nursing homes with many differently qualified healthcare workers teams is lacking. Consequently this means that the older people suffering from highly complex health problems are cared for by a large number of staff with limited professional knowledge [2]. More specifically, this lack of competency may lead to delayed, improper and inefficient assessments and treatment of medical problems in complex situations such as pain in people with dementia. The largest group of Swiss healthcare workers in nursing homes, 60%, are healthcare assistants and only 27% nursing staff are qualified nurses [33]. It is therefore necessary to provide a communication and information environment that allows healthcare workers at assistant and secondary level to rapidly share observations, accurately and easily with healthcare professionals to initiate decision-making processes. A number of studies of quality of care in nursing home suggest that these measures are inadequately implemented in everyday clinical practice [2, 8, 34, 35]. The research question is therefore: does a nursing-led intervention reduce pain intensity and pain duration for dementia patients living in nursing homes?

Following this research question, the study aim is to identify care needs of people with dementia suffering from pain living in a nursing home. Primary outcomes are pain intensity and pain duration of people with dementia. Secondary outcomes include: differences in pain assessments between healthcare worker groups, behavioural problems, the use of psychopharmacological drugs, and the use of analgesics.

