Sustainability and veracity of the interventions are ensured by following the comprehensive evaluation process based on Dobbins [45] that consists of:assessment of the accuracy between the conducted intervention and the study protocol: 50% of the intervention protocols are tested for compliance with the study protocol based on selected pain management strategies and structured communication skills (ISBAR, SOPIER, prompt initiation of medical prescriptions, usage of non-analgesic pain management strategies) by descriptive analysis.evaluation of operating procedures that are associated with pain managementquestioning of acceptability of the interventions carried out for all health care workers with a scale from 0 (= no acceptance) to 10 (= fully accepted)compliance (adherence) of interventions for all health care workers with a scale from 0 (= no adherence) to 10 (= complete adherence)assessment of the potential for change in clinical practice among healthcare workers with a scale from 0 (= no conversion potential) to 10 (= complete transformation possible)assessment of potential change in the management of pain among health care workers with a scale from 0 (= no change in potential) to 10 (= comprehensive amendment potential)

Pain as primary outcome is measured in all people with dementia in the comparison and intervention groups by means of:pain events per shift and per week;degree of pain intensity per work shift, per week day;pain-free intervals.

Secondary outcome variables will be measured by:frequency of behavioural problems (Neuropsychiatric Inventory NPI [46]);number/dosages of psychotropic drugs;Number/dosages of analgesics.

The documentation regarding the assessment of pain by nurses is always done in duplicate, by a health care worker on different education level. Tertiary outcome variables will be measured by:changes in the assessment of pain by healthcare worker on healthcare assistant level andchanges between the two healthcare worker groups on healthcare assistant level and registered nurse level.

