Hypotheses for primary outcomes are:H_a1_: There is a 20% reduction in pain events over time before and after the intervention and between intervention and comparison groups among nursing home older people.H_a2_: There is a 50% reduction in pain intensity over time before and after the intervention and between intervention and comparison groups among older people.H_a3_: There is a 20% reduction in the duration of pain free intervals over time before and after the intervention and between intervention and comparison groups among older people.

Furthermore the following hypotheses will be explored:There is a difference in the behavioural problems score (NPI) before and after the intervention and between intervention and comparison groups among older people.There is a difference in the psychopharmacological drug numbers/dosage before and after the intervention and between intervention and comparison groups among older people.There is a difference in the numbers/dosage of painkillers before and after the intervention and between intervention and comparison groups among older people.There is a difference in pain assessment over time before and after the intervention and between intervention and comparison groups among nursing home older people.There is still a difference in pain assessment by healthcare workers on assistant level over time before and after the interventionThere is still a difference in pain assessment between healthcare workers on assistant level and registered nurses level over time before and after the intervention.

The sample size used in the trial is determined based on the requirements of event history analyses and multilevel analyses to test the mentioned hypotheses.

Event history analyses: The required number of events for a two-tailed test of individual coefficients within a Cox model with other covariates has been calculated based on the method of Hsieh and Lavori [41]. A total of *n* = 179 people and 121 events are required for a power of 0.8 and a significance level of 0.05 based on an expected hazard ratio of 0.6 (SD 0.5), a probability of occurrence of 0.75 and a drop-out rate of 10%. Both the number of people and the number of events determined in the intended study protocol can be collected.

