**Fig. 3 Fig3:**
[figure not shown]
Time schedule

The actual data collection will be done by a study nurse with a BSc in Nursing. Potential confusions/problems with the raw data are discussed within the respective healthcare institution and with the leader of the study. Ambiguities with the procedure of data collection are discussed with the head of project management within the research team who also keeps a research diary. The study nurse transfers the anonymised data to the project management after the third measuring cycle. Two other study nurses enter the data into SPSS and carry out data cleansing before proceeding with the data analysis. The data of the comparison group are disclosed to the project management “PID” in encrypted form by the project manager “ZULIDAD”.

Data analysis will be performed using the IBM software programme SPSS® (version 24). The socio-demographic data are analysed descriptively (frequencies, central tendencies, standard deviations) and the outcome variables as follows:Pain intensity, duration and pain-free intervals are investigated in all dementia patients of the comparison and intervention group measuring the average duration of pain events per work shift (each work shift lasts 8.25 h) and per weekday, and the average degree of pain intensity per work shift, per work day as well as the duration of pain-free intervals with multilevel and events history analyses based on the data observation intervals T0, T1, T2.For the multilevel analyses (linear mixed models) over time, two levels are considered: the dementia patient and the healthcare institution. The event history analyses use cluster-adjusted Cox regressions. Furthermore, event history analyses will focus on evaluating the influence of the two nursing professional groups (at assistant/secondary and tertiary level), the pain pharmacotherapy (number and dosage), behavioural problems (NPI) and the psychopharmacotherapy (number and dosage).

A change in the assessment of pain by the healthcare workers is checked with interrater reliability tests. By means of the interrater reliability test, a potential variation between the two nursing groups on assistant/secondary and tertiary level is monitored.

To ensure the quality of data analyses, each data analysis step is independently checked by three different people.

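### The primary outcome is defined differently across the protocol article: pain duration is named primary but has no hypothesis, and H_a3 points the wrong way

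*Protocol article*

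**What the plan says.** The protocol article defines the primary outcome in four places.

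- **Background, aim and outcomes:** "Primary outcomes are pain intensity and pain duration of people with dementia". The research question just before it asks about the same two quantities.
- **Methods, outcome measures (after Fig. 2):** pain as primary outcome, in both groups, is measured by "pain events per shift and per week;degree of pain intensity per work shift, per week day;pain-free intervals". Pain duration is not on this list.
- **Methods, hypotheses:** under "Hypotheses for primary outcomes are" come three statements. H_a1 reads "There is a 20% reduction in pain events over time before and after the intervention and between intervention and comparison groups", H_a2 reads "There is a 50% reduction in pain intensity over time before and after the intervention and between intervention and comparison groups", and H_a3 begins "There is a 20% reduction in the duration of pain free intervals over time before and after the intervention".
- **Methods, data analysis (after Fig. 3):** "Pain intensity, duration and pain-free intervals are investigated in all dementia patients of the comparison and intervention group". The mean length of pain events within a shift is analysed; a count of events is not named.

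Two further places bear on the point. The opening paragraph of Methods lists pain duration and pain intensity among the data shared with the comparison study, and names the same two for the historical sample from the last documented assessment. Neither statement mentions pain events or pain-free intervals. The sample size paragraphs use a two-sided 0.05 and power 0.8 for one Cox coefficient (121 events, 179 people), and the same level and power for the mixed model (about 47 persons).

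**The concern.** A reader cannot tell from the article which outcome decides the trial. One of the two outcomes in the research question has no stated hypothesis. One of the three hypotheses, read literally, predicts that residents will do worse. Two of the three make between-group claims on outcomes that the description of the comparison data does not list.

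With several candidate lists in print, the main result could be chosen after the data are seen, and whichever outcome came out favourably could be matched to some part of the text. The article also says that the trial was registered retrospectively, so a single fixed definition in the protocol carries more weight than usual.

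**Working it through.** **1. The lists side by side**

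| Place | Intensity | Duration of pain | Pain events | Pain-free intervals |
|---|---|---|---|---|
| Background, primary outcomes | yes | yes | no | no |
| Methods, outcome measures | yes | no | yes | yes |
| Methods, primary hypotheses | yes (H_a2) | no | yes (H_a1) | yes (H_a3) |
| Methods, data analysis | yes | yes | not named as a count | yes |
| Methods, comparison-group data | yes | yes | not listed | not listed |

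Only intensity appears in every row. The outcome measures and the hypotheses agree with each other. The Background and the data analysis text each differ from them and from one another.

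**2. Direction of H_a3**

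The research question asks whether the intervention reduces pain. A shorter pain-free interval means that pain returns sooner. H_a3 predicts a 20% shortening, the opposite of benefit. It may be a misworded hypothesis about pain duration or a slip for an increase; the text does not settle which.

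**3. What the stated sample size covers**

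Inputs from the event history paragraph: hazard ratio 0.6, covariate SD 0.5 (variance 0.25), two-sided 0.05, power 0.8, event probability 0.75, dropout 10%.

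- Events = (1.960 + 0.842)² / (0.25 × (ln 0.6)²) = 7.849 / (0.25 × 0.2609) = 120.3, rounded up to 121.
- People = 120.3 / 0.75 = 160.4, rounded up to 161; 161 / 0.90 = 178.9, rounded up to 179.

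Both stated figures are reproduced. They are the requirement for one test at the full 0.05, with no allowance for several hypotheses.

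**4. Error rate if any one hypothesis sufficed**

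- Three independent tests at 0.05: 1 − 0.95³ = 14.3%, counting results in either direction.
- Favourable direction only: 1 − 0.975³ = 7.3%.
- The article gives no correlation between the outcomes. Simulating three normal statistics with an assumed common correlation of 0.3, 0.5, 0.7 and 0.9 gives 13.6%, 12.5%, 10.9% and 8.3% in either direction.
- If the before-after and between-group parts of each hypothesis were counted as separate tests, six independent tests would give 1 − 0.95⁶ = 26.5%, falling to 10.8% at a correlation of 0.9.

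**The case against.** Several parts of the opposing case are sound.

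- **A reader might infer that pain duration is never tested.** The document does not support that. The data analysis text analyses the length of pain events with multilevel and event history models. What is missing is a hypothesis, not an analysis.
- **A reader might infer that events and pain-free intervals have no primary status.** They lack it only in the Background; the outcome list in Methods calls them primary.
- **A reader might infer an unadjusted analysis with a 26% error rate.** The 0.05 is a sample size input. The article does not say that each hypothesis will be declared at 0.05 or that one success is enough, and an analysis plan that is not shown may settle this. The 26% also needs six independent tests, each counted alone. The wording of each hypothesis reads as naturally as one joint claim or one group-by-time term, which leaves three tests. A rule that all three must succeed would remove the inflation.
- **Time in pain and pain-free time may be two measures of one construct.** This is the best defence of the differing lists. But the data analysis text lists both, so it treats them as distinct, and the direction of H_a3 would still be wrong.
- **The list of comparison data may not be exhaustive.** That is possible, since the outcome list says that all measures are taken in both groups. The two statements still need to be reconciled.
- **Choosing intensity is partly a preference.** This stands. The Background gives duration equal standing, and duration is also listed for the comparison group. Intensity has the advantage of appearing everywhere.

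None of this removes the contradiction. An unseen plan could add a multiplicity rule, but it could not agree with all the printed definitions.

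**Conclusion.** The point holds as an inconsistency in the definition of the primary outcome. It rests on the text alone and not on any assumption about an unseen plan. Pain duration lacks a hypothesis, H_a3 contradicts the research question, and the between-group claims in H_a1 and H_a3 reach beyond the pain variables listed for the comparison group.

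The multiplicity part is conditional. If any one of the three hypotheses sufficed at 0.05, the chance of at least one false positive in either direction would be at most about 14%, and about 8% at an assumed correlation of 0.9. It would be higher only if the two contrasts within each hypothesis were counted separately, which the text does not require. The correction should be made because it changes what the trial can conclude and is cheap.

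**What to change.** 1. Use one primary outcome list in the Background, the outcome measures, the hypotheses and the data analysis text.
2. Name pain intensity as the primary outcome, with one prespecified contrast at two-sided 0.05, for example the group-by-time term at T2. Confirm that the comparison data support the chosen contrast.
3. Add a hypothesis for pain duration. Test duration, then pain events, then pain-free intervals in that fixed order as key secondary outcomes.
4. Make between-group claims only for outcomes that the comparison data contain, and reconcile the description of those data with the outcome list.
5. Correct the direction of H_a3 or, if pain duration was meant, reword it.
6. State which sample size calculation supports the primary outcome. For intensity this would presumably be the mixed model calculation (about 47 persons) and not the Cox calculation (179 people). Say how its regression coefficient of 1 relates to the 50% reduction in H_a2.

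The cost is amendment wording and a restated sample size paragraph, with no new data. A fixed order needs no split of the 0.05. The downside is that later outcomes are confirmatory only if the earlier ones succeed.

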## Methods

We employ a quasi-experimental nursing-led intervention trial with a repeated measures design [36] based on a convenience sample of four nursing home clusters and a total sample of 411 dementia patients. All dementia patients in the comparison group will be obtained from the Zurich Life And Death with Advanced Dementia (ZULIDAD) Study [37]. The ZULIDAD data were collected from people with dementia (men and women), who are older than 70 years in one nursing home (*n* = 150), in 2015. Data between intervention sites and comparison site are similar because the same assessment instruments were used, based on an older person assessment instrument, and include pain duration, pain intensity, behavioural problems, differences of psychopharmacological drugs, and differences of analgesics. The comparison can be made with data from the first day and from the 49^th^ of each data collection phase (t0, t1, t2) and with a historical sample of pain duration and pain intensity from the last pain assessment documented in the older person Assessment Instrument Data (RAI) of each participant.

People with dementia in the intervention group will be are recruited in three healthcare institutions in the cantons of Thurgau and Zurich.

All healthcare workers from these three intervention institutions are included in the study, trained and coached in the provision of interventions. The following inclusion criteria apply to healthcare workers:must be at least 18 years old;must have been employed at least 12 months in the respective organisation;must work for at least 30% of a working week;be able to communicate in German.

The collection of data will take place in three nursing homes in the Canton of Thurgau and in the Canton of Zurich. For the comparison group, data from the ZULIDAD study [37] will be used.

All older people are screened for eligibility to participate in the study. Recruitment is described in Fig. 1. Only older people with documented nursing-initial-assessment symptoms of dementia are included in this intervention trial by author no. 3.

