Multilevel analyses (linear mixed models): The required number of cases for basic evaluations using multilevel models/linear mixed models have been determined by the approximation method [47] - with equal power and significance level as in the event analyses. This approach recognises a random intercept model with covariates that only vary between older people (treatment). In order to carry out only two repeated measurements per person, approximately *n* = 47 persons are required using a regression coefficient of 1 and a standard deviation of 0.5.

There are three data monitoring cycles (T0, T1, T2) and two intervention cycles (I1, I2) to measure the primary and secondary outcomes, see Fig. 3. Each data monitoring cycle extends over 7 weeks (=49 days) and includes seven different weekdays and at least three different work shifts. The data are extracted from the older people’ specific pain diaries (degree of pain intensity), which are kept separately from conventional nursing documentation. For the description of the sample, socio-demographic data on age and gender are collected from all participants. Additional data on qualifications and professional experience are collected from nursing staff, and care needs, dementia type and severity of dementia from people with dementia.

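### The data named for the comparison with the historical group (days 1 and 49 of each phase, plus one RAI record) cannot supply the weekly event counts and pain-free intervals that H_a1 and H_a3 test between groups

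*Protocol article*

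**What the plan says.** All places are in the Methods section of the protocol article.

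- **Comparison group paragraph.** "The comparison can be made with data from the first day"; the other day named is day 49, in every phase. A second source is one RAI pain record per participant, the most recent on file. The same paragraph lists what the intervention and comparison sites have in common: pain duration, pain intensity, behavioural problems, psychopharmacological drugs and analgesics. Pain events and pain-free intervals are not on that list. The comparison data come from one nursing home (n = 150) and were collected in 2015.
- **Primary outcome list.** Pain is to be measured in both groups as "pain events per shift and per week", as intensity per shift and weekday, and as pain-free intervals.
- **Hypotheses.** H_a1 (events), H_a2 (intensity) and H_a3 (pain-free intervals) are each stated both before against after and between groups.
- **Data collection.** "Each data monitoring cycle extends over 7 weeks (=49 days) and includes seven different weekdays and at least three different work shifts". Ratings are taken from "specific pain diaries (degree of pain intensity), which are kept separately from conventional nursing documentation".
- **Data analysis.** Intensity, duration and pain-free intervals are analysed in both groups by multilevel and event history methods, "based on the data observation intervals T0, T1, T2", with no restriction to particular days.

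**The concern.** The paragraph on the comparison group is the only place where the article says which data carry the contrast with the historical controls. What it names is two single days per phase and one routine record. The outcome list, the hypotheses and the analysis paragraph ask the same contrast to deliver a weekly count and an interval length.

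If both are followed, two of the three primary hypotheses contain a between-group claim that the named data cannot test in full. The analyst would then have to decide, with data in hand, which days and measures enter the comparison. A reader of the results could not tell whether a between-group statement on events or pain-free intervals rests on comparable observation.

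**Working it through.** **Inputs from the article.** Cycle length 49 days; three cycles; at least three shifts a day, each 8.25 h; comparison on days 1 and 49 plus the last RAI record; total sample 411, of whom 150 are taken as the comparison group; mixed-model sizing of about n = 47 with two measurements per person, coefficient 1, SD 0.5, power 0.8, alpha 0.05.

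**Step 1: share of days named for the comparison.** 2/49 = 4.1% per cycle, or 6 of 3 × 49 = 147 days over three cycles. With three ratings a day (an assumption, as the article says at least three) this is 18 of 441 ratings; the share is the same.

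**Step 2: what two days can give.**
- Events per shift and intensity per shift: obtainable.
- Events per week: not obtainable. Days 1 and 49 are 48 days apart and contain no complete week.
- Intensity by weekday: two weekdays per resident. Since 48 mod 7 = 6, day 49 is the weekday before that of day 1.
- Pain-free interval: visible only within the day, so cut off at about 24 h (3 × 8.25 = 24.75 h of shift time).

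**Step 3: what the RAI record adds.** One record of pain duration and intensity per participant. It supplies neither a weekly event count nor a pain-free interval.

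**Step 4: consequence by hypothesis, between-group part only.**
- H_a1: weekly counts have no data. Per-shift events exist on two days in the intervention homes, but nothing in the article shows them for the comparison home.
- H_a2: intensity is held on both sides.
- H_a3: intervals are truncated in the intervention homes and not shown to exist in the comparison home.

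**Step 5: precision.** The article gives no variance components. Resident variance 1 and residual variance 1 are assumed because, with SD 0.5 read as that of the treatment covariate, they reproduce its sample size: (1.960 + 0.842)² × (1 + 1/2) / (1² × 0.5²) = 7.849 × 1.5 / 0.25 = 47.1, stated as about 47.

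Take 411 − 150 = 261 intervention residents, one record per comparison resident (variance 1 + 1 = 2), independent days and no between-home variance:
- Two days: (1 + 1/2)/261 + 2/150 = 0.00575 + 0.01333 = 0.0191; SE 0.138.
- All 49 days: (1 + 1/49)/261 + 2/150 = 0.00391 + 0.01333 = 0.0172; SE 0.131.
- Reduction in variance: 1 − 0.0172/0.0191, about 10%.

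The comparison term, 0.01333, does not change, which is why the gain is small.

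**The case against.** The best defence is that the sentence is permissive, follows the description of the ZULIDAD data and concerns only the historical comparison. The analysis paragraph already bases the T0/T1/T2 analyses on the whole intervals. The two days may have been chosen to match what the comparison study recorded, and a condensed article may leave such detail to the full protocol.

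Much of this stands, and it rules out two stronger readings that a reader might infer.

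- **That the plan throws away about 96% of the diary ratings.** The figure is only the complement of 4.1%. The article does not say that the other days go unused; they remain available for the before-after analysis in the intervention homes.
- **That the two-day wording inflates the variance of change about 25-fold.** With the unit variances, the variance of a cycle-to-cycle change is 2 × 1/2 = 1.00 with two days and 2 × 1/49 = 0.04 with 49. But that is change within the intervention homes, which the comparison sentence does not govern, and it assumes independent days. With an assumed first-order autocorrelation of 0.8, the 49-day value is about 0.33.

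Nor can one say that two primary measures are wholly undefined, since per-shift events survive and pain-free intervals are truncated rather than absent. That only two weekdays appear in the whole sample would need a common start date, which the readable text does not give.

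The defence does not remove the conflict. No other basis for the between-group contrast is offered, and the article does more than omit detail: it assigns to both groups outcomes that the named comparison data do not contain.

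**Conclusion.** The point holds as a contradiction about which outcomes can be compared between groups. As written, the between-group part of H_a1 on weekly counts, and that of H_a3 for intervals longer than about a day, lack usable data. H_a2 is not affected in this way, and neither are the before-after analyses on the full diaries.

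Loss of precision is a minor part. The gain of about 10% in variance rests on 261 against 150 residents, one record per comparison resident, unit variances and independent days. It ignores variance between homes, which with a single comparison home could outweigh it. Using all 49 intervention days would not by itself make weekly events or pain-free intervals comparable, because the comparison home is not shown to have shift-level diaries. If it does have them, the restriction on H_a1 and H_a3 falls away and only the wording needs repair.

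**What to change.** Reconcile the comparison group paragraph with the outcome list, the hypotheses and the data analysis paragraph.

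1. State that the day-1 and day-49 wording applies at most to the historical comparison, and that all T0/T1/T2 contrasts in the intervention homes use the full 49-day diaries.
2. Limit the between-group primary tests to the measures the comparison home actually holds, namely pain intensity and pain duration. Reword H_a1 and H_a3 so that weekly events and pain-free intervals are tested before against after only, unless the comparison home is confirmed to have shift-level diary data.
3. For the between-group test, summarise the intervention-home data over the same kind of observation window as the comparison record, and state that window. The article does not give the one behind the RAI item, so it has to be taken from the instrument.

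The cost is wording and data preparation. The diaries are already kept for the full cycle, so no further data collection is needed.
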